## Abstract

**Background:**

The importance of staying active instead of bed rest has been acknowledged in the management of musculoskeletal disorders (MSDs). This emphasizes the potential benefits of adjusting work to fit the employee's remaining work ability. Despite part-time sick leave being an official option in many countries, its effectiveness has not been studied yet. We have designed a randomized controlled study to assess the health effects of early part-time sick leave compared to conventional full-day sick leave. Our hypothesis is that if work time is temporarily reduced and work load adjusted at the early stages of disability, employees with MSDs will have less disability days and faster return to regular work duties than employees on a conventional sick leave.

**Methods/Design:**

The study population will consist of 600 employees, who seek medical advice from an occupational physician due to musculoskeletal pain. The inclusion requires that they have not been on a sick leave for longer than 14 days prior to the visit. Based on the physician's judgement, the severity of the symptoms must indicate a need for conventional sick leave, but the employee is considered to be able to work part-time without any additional risk. Half of the employees are randomly allocated to part-time sick leave group and their work time is reduced by 40–60%, whereas in the control group work load is totally eliminated with conventional sick leave. The main outcomes are the number of days from the initial visit to return to regular work activities, and the total number of sick leave days during 12 and 24 months of follow-up. The costs and benefits as well as the feasibility of early part-time sick leave will also be evaluated.

**Conclusion:**

This is the first randomised trial to our knowledge on the effectiveness of early part-time sick leave compared to conventional full-time sick leave in the management of MSDs. The data collection continues until 2011, but preliminary results on the feasibility of part-time sick leave will be available already in 2008. The increased knowledge will assist in better decision making process regarding the management of disability related to MSDs.

**Trial Registration:**

International Standard Randomised Controlled Trial Number Register, register number ISRCTN30911719

## Background

Evidence is increasing on the importance of staying active instead of bed rest in the management of musculoskeletal disorders (MSDs) and related disability [1-4]. It has been recommended that total absence from work due to non-specific back pain should be avoided because of its possible delaying effects on recovery [5]. In reducing absence from work due to MSDs or other pain-related conditions, workplace-based return-to-work interventions have shown to be effective [6]. The evidence is particularly strong for offers to accommodate work during recovery and contacts between healthcare provider and the workplace.

In a Finnish survey, employees with health problems were asked to assess their ability to work prior to visiting an occupational health (OH) physician [7]. The results showed that employees with MSDs report partial work ability almost twice as often as complete inability to work (28% vs. 16%). In the same survey, both employees with MSDs and their physicians often regarded work-related interventions as potentially beneficial to improve recovery. The importance of these interventions is further supported by the evidence on the significance of work-related factors in the aetiology of MSDs [8].

Employees with partial work ability could be encouraged to stay at work instead of taking sick leave. It requires, however, flexible systems to adjust work load in order to accommodate the employee until the disability has improved. Part-time sick leave system in Finland enables the employee to work 40–60% of the daily working time but only after the full-time sick leave has lasted for almost three months. In most cases, part-time sick leave is economically more rewarding than total absence from work since, in addition to the salary for the worked hours, the Social Insurance Institution provides the employee a monetary compensation, which is half of that for full-time sick leave. So far, part-time sick leave has been used, however, less than expected.

In some other countries (e.g., Sweden, Norway, Denmark), taking part-time sick leave is allowed without any preceding full-time sickness absence. Yet, the effectiveness of part-time sick leave has been poorly studied. A Norwegian cluster-randomised study on "active sick leave" (return to adjusted work supported by social security after conventional sick leave had lasted 16 days or more) showed no beneficial effects, partly because part-time sick leave system was so seldom used [9]. Users' contentment seems to be, however, high; 92% of employees on part-time sick leave in a Swedish survey were satisfied with the arrangement [10]. Two-thirds of those on full-time sick leave considered part-time sick leave as a potentially good alternative for them. Yet, some disadvantages have also been detected: a Swedish study with a follow-up of 1.5 years found that part-time sick leaves tended to last longer than conventional sick leaves [11]. The authors concluded that the effectiveness of part-time sick leave should be studied in a randomized setting.

This randomized controlled study was designed to assess the health-related and economical effects of early part-time sick-leave compared to conventional sick leave in employees with MSDs.

## Methods/Design

### Identification and eligibility of study participants

The study will be performed in several OH units of medium sized and large private or public enterprises, in which the employees are known to be exposed to physically strenuous or static work tasks (Figure 1). Employees who seek medical advice primarily due to musculoskeletal pain in the neck or shoulder region, back, or upper or lower extremities are eligible to the study. The symptoms and related disability must warrant prescription of full-time sick leave according to the current practice, but the physician considers the employee to be able to work part-time without the risk of the health condition to deteriorate. Table 1 shows the inclusion and exclusion criteria.

**Figure 1 F1:**
[figure not shown]
Study design.

**Table 1 T1:** Eligibility of the participants

**Inclusion criteria**
- 18 to 60 years of age
- permanent or long-term employment (30 hours or more per week)
- no sick leave or other absence exceeding two weeks during the preceding month
- not more than 30 days on sick leave due to any health problem during three preceding months
- employee is not listed for any surgery that requires more than one week of sickness absence
- no plan for longer absence from work during 12 months after enrollment
- an employee can be enrolled only once
**General exclusion criteria**
- acute infections
- major accidental injury
- active inflammatory arthritis
- suspected occupational injury or disease
- malignant tumour diagnosed or treated during the preceding year
- severe mental disorder
- pregnancy
- severe pain (> 7 on a scale from 0 to 10)
- pain interferes with sleep severely (> 7 on scale from 0 to 10)
**Pain area specific exclusion criteria**
Back region:
- muscle weakness in the lower extremities related to back pain
- positive straight-leg-raising test
- pain-related trunk list
- painful spasm of the back when bending forward
Neck and shoulder region:
- muscle weakness in the upper extremities related to the pain
- head compression or movements induce radiating pain below elbow level
- painful torticollis
Shoulder and upper extremity regions:
- muscle weakness related to the pain
- severe pain in movements interfering with most functions
Lower extremities:
- pain prevents walking

### Interventions

During the initial visit, the OH physician will inform the employee about the study and its aims. If the employee agrees to participate, informed consent will be signed. It includes a permission to contact the supervisor, preferably during the same visit, in order to verify whether the work-related arrangements for part-time sick leave are feasible, in case the employee is allocated to the intervention group. If the supervisor disagrees, the employee will be excluded from the trial.

Once the agreements from the employee and the supervisor have been obtained and before the randomisation has occurred, the physician will determine the length of the sickness absence based on symptoms (Table 2), clinical findings [12,13] and background information (Table 3). If the employee is allocated to part-time sick leave (intervention group), daily work load will be reduced by restricting work time. Also, if necessary, remaining work tasks will be modified so that working should be possible despite the symptoms. In the control group, work load will be eliminated with full-time sick leave. Both groups will receive appropriate medical advice, and the need for medical treatments and a control visit will be determined as usual.

**Table 2 T2:** Health-related variables inquired at baseline and during follow-up

**Outcome**	**Measure**
Main reason for the visit (at baseline)	Localisation and characteristics of pain
Pain intensity	Scale from 0 to 10
Interference with work activities	Scale from 0 to 10
Interference with sleeping	Scale from 0 to 10
Self-assessed functioning	Oswestry Back questionnaire [15] Quick DASH (Disabilities of the Arm, Shoulder and Hand) [16] COAT (Comprehensive Osteoarthritis Test) for lower extremities [17]
Productivity at work	Quantity and Quality of work [26]
Adjustments at work (during follow-up)	Description of change in physical work load (structured and open questions)

**Table 3 T3:** Explanatory variables measured at baseline

**Assessments by physician**	
Physical examination	Standardised protocol [12, 13]
Weight	Self-reported
Height	Self-reported
**Health-related background information**	
Diabetes, cardiovascular diseases	Interview by physician
Previous sick leaves	OH data base
Depression	Questionnaire [20]
Quality of life	EQ-5D [21]
**Physical work load factors**	
Handling of loads, repetitive movements, use of hand tools, awkward postures at work	Questionnaire [18, 19]
**Background variables**	
Company	Questionnaire
Occupation	
Main work tasks	
Education	
Job seniority	
Work hours	
Commuting time	
Age	
Gender	
Marital status	
Smoking	
Alcohol consumption	
Physical exercise	
Psychosocial risk factors	Adapted from Copenhagen Psychosocial Questionnaire [22]
Fear avoidance	Questionnaire [23]
Procedural and relational justice	Questionnaire [24]
Effort-reward imbalance	Questionnaire [25]

In the following day after the initial visit, those allocated to part-time sick leave will return to work for 40 to 60% of their regular working hours. They are asked to give their supervisor a statement from the physician indicating the duration of part-time sick leave, what kind of work loads are allowed and which are not recommended, and if any additional work adjustments are needed. If the reduction of work time cannot be organised on a daily basis, the employee may work every second day for the whole day and every second day stay at home.

When the sick leave is over, employees in both groups return to regular work. Those who are unable to resume regular work activities will be re-evaluated by an OH physician, who can prescribe either full-time sick leave or continue part-time sick leave, according to the physician's clinical judgement. The length of sick leave will be determined as usual.

If the employee in the part-time sick leave group needs full-time sick leave, part-time sick leave cannot be applied again after full-time sick leave has ended. Return to part-time sick leave is possible in a situation when the health problem relapses within one month after the employee has returned to regular work. The total maximum length of the part-time sick leave is two months. Participation in the study intervention does not affect the employee's right to general social security benefits. Neither does it have any financial effect to the employee, because he or she receives the same compensation (regular salary) during part-time and full-time sick leave. The employer will start receiving compensation after the sick leave has lasted for 10 working days.

### Objectives

Musculoskeletal symptoms typically deteriorate during the work day and towards the end of the work week, and they resolve during break, night rest and weekend [14]. Our hypothesis to be tested in the current study is that employees whose work time is temporarily reduced and work load adjusted during early stage of disability will have less disability days and faster return to regular work duties than employees on conventional sick leave.

### Outcomes

The main outcomes are the number of days from the initial visit to the return to regular work activities and the total number of part- and full-time sick leave days during one- and two-year follow-up. Other outcomes are changes in symptoms as well as in self-assessed functioning during follow-up [15-17].

Data on self-assessed workload will be collected after the initial visit and during part-time sick leave in order to recognise physically strenuous work tasks relevant to MSDs [18,19], as well as to list the work adjustments made during the part-time sick leave. This will be included in an internet based questionnaire together with the symptoms and background variables [20-25]. The questionnaire will be sent to the employees immediately after recruitment and at one, three, eight, 12 and 52 weeks. Those without access to internet will be telephone-interviewed by a researcher. Also, the supervisors in both groups will be interviewed by phone after the employee has returned to work.

Participating employees, their supervisors, OH personnel, human resources management, as well as occupational safety and trade union representatives will be interviewed, and the feasibility of early part-time sick leave will be evaluated based on the qualitative information collected in the interviews. From those employees, who decline to participate, only information on age and gender will be collected. They will also be offered a possibility to provide the main reason for not participating. This can be done with an anonymous questionnaire that can be returned in a closed envelope directly to the researchers. The reason for a negative response from the supervisor is also documented.

The follow-up is extended to two years with the purpose of detecting the possible longer-lasting effects on e.g. illness behaviour. One and two years after the initial visit, the dates and diagnoses of all sickness absences (including those prescribed outside OH services) will be collected from the OH units.

Patient enrolment started in January 2008 and it is planned to last until July 2009. Follow-up of the last participants will finish two years later in 2011. Based on the pilot study, however, preliminary results on the feasibility of early part-time sick leave will be available already in 2008.

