### Statistical methods

A survival analysis will be used to study the time to return to work in the intervention and control group. The amount of sick leave days will be analysed at 12 and 24 months, and the associations between the outcomes and background variables will be analysed using general linear models. In addition, the change in symptoms and disability indices will be studied at various time points using general linear models for repeated measurements.

Subgroup analyses will be performed in relation to patient compliance, type of work, adequacy of work adjustments, previous sick leaves, pain characteristics (such as localisation, duration), and level of disability at baseline. All analyses will be made based on an intention-to-treat principle.

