## Discussion

The target of this intervention is to adjust work (both work time and demands) to accommodate the disabled employee so that he or she can continue working during recovery from a MSD. As pointed out by Durand et al [27], in this type of intervention work becomes an object of the intervention itself raising various methodological challenges. In addition to the medical judgement by the physician, the intervention requires actions and decisions made by the employee, supervisor, colleagues and employer – each with their own values, objectives, interests, and training [28].

Sickness absence is usually considered as a consequence of a health disorder rather than its treatment and, therefore, in most studies, it has been used as an outcome measure. In this trial, however, the mode of sick leave (part- or full-time) is used as an intervention to affect the outcome, i.e., the quantity of sick leave (number of sick leave days). The potential benefit of the intervention, i.e., the difference in the total number of full- or part-time sick leave days between the intervention and control group, will arise either from the employee's decision to return to regular work earlier than recommended by the physician, or from the need for additional part- or full-time sick leave during the follow-up period.

It is essential in this intervention that the physician determines the length of the disability before allocation, and adheres to this when prescribing either part- or full-time sick leave. This is to avoid bias that might occur if the length of the sick leave is determined differently for part- and full-time sick leave. The risk for bias concerns also the possible control visit, during which the allocation to further part- or full-time sick leave is again open to both the physician and the employee. Inappropriately timed return to regular work in either group should, however, show in secondary outcomes, such as pain, functional status, employee satisfaction and costs.

Despite the extensive amount of quantitative data collected in this trial on individual, ergonomic, psychosocial and economic factors, we do not have the means to quantify all the aspects of the arrangements made at the workplaces during part-time sick leave. Acknowledging the potential effect of this contextual process on the outcome of the intervention, we aim to collect all relevant qualitative data during the study from the employee and the supervisor.

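### The main count of sick leave days is unweighted: it measures days away from regular work, not working time lost, and it lacks a counting rule for alternate-day part-time leave

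*Protocol article*

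**What the plan says.** The Outcomes section of the protocol article names two main outcomes: time from the initial visit to regular work, and "the total number of part- and full-time sick leave days during one- and two-year follow-up". The Discussion describes the potential benefit as "the difference in the total number of full- or part-time sick leave days between the intervention and control group". Neither place gives a weight for hours worked, so the plain reading is a one-for-one sum.

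The two kinds of day differ in content. In the Interventions section (text after Table 3), employees on part-time leave "will return to work for 40 to 60% of their regular working hours". For controls the same section says "In the control group, work load will be eliminated with full-time sick leave". If hours cannot be cut daily, "the employee may work every second day for the whole day and every second day stay at home". The article does not say how the days of that arrangement enter the count.

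Three other statements bear on the point:
- The length of leave is set before randomisation (Interventions).
- The hypothesis concerns disability days and return to regular duties (Objectives).
- The costs of lost working time are analysed separately (Economic evaluation).

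**The concern.** Part-time days arise by design in the intervention arm. The sum therefore adds days with about half the hours worked to days with none, and the mix differs by arm. A reader who sees more sick leave days in the part-time arm may conclude that more work was lost, when less was. The Background shows that this is not far-fetched: an observational follow-up in Sweden "found that part-time sick leaves tended to last longer than conventional sick leaves".

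The alternate-day arrangement raises a second problem, which runs the other way. If absence records show only the days at home, an employee with the same prescription as a control shows half as many days. A main outcome would then depend on how a workplace schedules the leave. This is part of the outcome's definition, not a modelling detail.

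**Working it through.** The plan gives no numerical target for sick leave days. Its sample size rests on the proportion back at regular work, so there is no figure to reproduce here.

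**Inputs.** Share of hours worked on a part-time day: w = 0.4 to 0.6 (Interventions). Share lost: 1 − w = 0.6 to 0.4. Share lost on a control's full-time day: 1 (Interventions). The day counts below are assumed for illustration.

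**1. General relation.** Let P be part-time days and F_I full-time days in the intervention arm, and F_C full-time days in the control arm.
- Difference in the plan's count: D = P + F_I − F_C.
- Difference in working time lost: L = (1 − w)P + F_I − F_C = D − wP.

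The two measures differ by wP. Whenever 0 < D < wP, the count shows more days and working time lost shows less. This also holds for totals over 12 or 24 months, where other absences enter F_I and F_C.

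**2. One episode, wholly part-time against wholly full-time.** Less work is lost as long as P(1 − w) < F_C, that is, P/F_C < 1/(1 − w).

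| Hours worked | Share lost | Break-even ratio |
|---|---|---|
| 40% | 0.6 | 1/0.6 = 1.67 |
| 50% | 0.5 | 1/0.5 = 2.0 |
| 60% | 0.4 | 1/0.4 = 2.5 |

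Take 14 part-time days against 10 full-time days. The count difference is +4. The differences in working days lost are:
- 40% worked: 14 × 0.6 − 10 = −1.6
- 50% worked: 14 × 0.5 − 10 = −3.0
- 60% worked: 14 × 0.4 − 10 = −4.4

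**3. Equal prescriptions, extra full-time leave later.** Both arms are prescribed 10 working days, and the part-time arm later takes extra full-time days. Then L = 10(1 − w) + extra − 10.

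| Extra full-time days | Count difference | L at 40% worked | L at 50% | L at 60% |
|---|---|---|---|---|
| 0 | 0 | −4.0 | −5.0 | −6.0 |
| 2 | +2 | −2.0 | −3.0 | −4.0 |
| 4 | +4 | 0.0 | −1.0 | −2.0 |

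The first row matters for interpretation. With identical prescriptions and no effect on recovery, the weighted measure already shows 40–60% less time lost on the initial leave.

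**4. Alternate-day leave.** A 10-working-day prescription taken on alternate days is 10 days if every working day of the arrangement counts, and 5 if only home days count. Against a control with 10 days, the difference is 0 or −5. If a share a of the intervention arm uses this form, the home-days rule shifts that arm's mean by −5a per 10 prescribed days. The article gives no value for a; the shift runs from 0 (nobody) to −5 (everybody). The home-days rule would also mix units within the arm, since those employees would be counted by time lost and the others by duration.

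**The case against.** The strongest reply is that the unweighted count is the quantity the trial means to test. The Objectives section speaks of disability days, and the Discussion treats the mode of leave as the intervention and the number of days as the outcome. Prescribed length is fixed before allocation, so initial counts are equal in expectation and a difference reflects early return or additional leave. This stands: the count is coherent and should remain the main outcome.

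It is also said that lost working time is already covered by the Economic evaluation. That section covers its cost, allowing for employer compensation. It does not give time lost as an outcome, so the reply stands only in part.

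A reader might infer more than the article supports:
- *That the sum is bound to move against the intervention.* The cited study was not randomised. Here the length is set before allocation and part-time leave is capped at two months in total. Reversal is possible, not predicted.
- *That any claim of less sickness absence should rest on hours-weighted days.* Row 0 of the second table shows why not: much of that advantage is created by assignment.
- *That leavers and long absences distort the count.* Eligibility requires "no plan for longer absence from work during 12 months after enrollment" while follow-up runs to 24 months, but bias between arms needs a difference between arms, and nothing in the article points to one. Handling of time employed is commonly left to a full protocol or SAP, which are not shown.
- *That a general linear model is wrongly fixed for the count.* The sentence beginning "The amount of sick leave days will be analysed at 12 and 24 months, and the associations between the outcomes and background variables" attaches that model most naturally to the associations, so the model for comparing days is not clearly stated.

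**Conclusion.** The point holds in a limited form. As defined, the outcome measures days not at regular work and cannot by itself show whether working time lost rose or fell. For a single episode the two measures disagree in sign between a length ratio of 1 and 1.67 (40% of hours worked) to 2.5 (60% worked). For totals they disagree whenever the count difference lies between 0 and wP. The episode ratios do not carry over as percentages to the 12- and 24-month totals, which include other absences and full-time days in the intervention arm.

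The alternate-day ambiguity is a factor of 2 for the employees concerned, and counting home days only would favour the intervention. Its effect on the arm mean depends on how many use that form, which is not given.

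These results assume that the sum is unweighted, as its wording implies, and that a part-time day has 40–60% of hours worked as prescribed. Neither issue invalidates the trial; both affect what may be concluded from a main outcome.

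**What to change.** 1. Keep the unweighted count as the main outcome and label it 'days not at regular work'.
2. State that every working day within an alternate-day arrangement, worked or at home, counts as one part-time day.
3. Pre-specify a supporting outcome, working time lost: a full-time day counts 1, and a part-time day counts the share of hours not worked. Report part-time and full-time days separately beside it. State that part of any difference follows from assignment itself and is not evidence of faster recovery.
4. Adjust the between-group comparison of days for the length prescribed before randomisation and for previous sick leave. The first is already determined for each employee (Interventions) and the second already collected (Table 3). This removes chance imbalance in two variables closely tied to the outcome.

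The cost is a few sentences of definition, one more reported outcome, and one data item. The share of hours worked must be recorded, because the Interventions section does not list it among the contents of the physician's statement.

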### Blinding

Due to practical and ethical reasons neither the employee nor the physician will be blinded to group assignment during the initial visit. Allocation is also open to the two interviewers and to the other possible physicians during later visits.

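### Scales taken only in the first questionnaire are post-allocation values labelled baseline, which can bias the secondary change analyses and the baseline-disability subgroup

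*Protocol article*

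**What the plan says.** The Outcomes section of the protocol article gives the only questionnaire schedule: "The questionnaire will be sent to the employees immediately after recruitment and at one, three, eight, 12 and 52 weeks". It describes the content as self-assessed workload, and adds "This will be included in an internet based questionnaire together with the symptoms and background variables [20-25" (the references cover depression, EQ-5D, psychosocial factors, fear avoidance, justice and effort-reward imbalance). It also fixes the timing against the visit: "Data on self-assessed workload will be collected after the initial visit and during part-time sick leave".

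On allocation, the Blinding section says that "neither the employee nor the physician will be blinded to group assignment during the initial visit". On the start of the intervention, the Interventions section says "In the following day after the initial visit, those allocated to part-time sick leave will return to work".

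The title of Table 2 (pain, interference with work and sleep, Oswestry, Quick DASH, COAT, productivity) and that of Table 3 (explanatory variables) both describe their contents as baseline. The Interventions section also states that "before the randomisation has occurred, the physician will determine the length of the sickness absence based on symptoms (Table 2), clinical findings", together with the Table 3 background information. Two of the Table 1 exclusions need a 0–10 score, one for pain and one for interference with sleep.

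In Statistical methods, "the change in symptoms and disability indices will be studied at various time points using general linear models for repeated measurements", and one listed subgroup factor is the degree of disability at baseline. The Economic evaluation counts the reduction of pain and disability on a 0–10 scale as a non-monetary benefit.

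**The concern.** A baseline value should be fixed before anyone knows the allocation. Otherwise it can respond to the allocation, and any analysis that treats it as the starting point can remove part of a real effect or create one that is not there.

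There are two routes here. The employee may answer with relief or disappointment about the allocated group. If the reply is delayed past the first day, the part-time group may also answer after working while the control group has been at home. The protocol makes the second route plausible: its Objectives section starts from the observation that musculoskeletal symptoms worsen with work and ease with rest.

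Three things are at stake. The first is the change analysis of symptoms and disability indices. The second is the disability reduction used in the economic evaluation. The third is the baseline-disability subgroup, which would be defined by a value taken after randomisation. The Discussion also relies on secondary outcomes such as pain and function to reveal a badly timed return to work in either group, so a compromised reference value weakens that check.

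**Working it through.** No stated figure in the article is in question, so there is none to reproduce. The check is one of timing, followed by the consequence for the analysis.

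**Order of events**

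1. At the visit, eligibility is checked (0–10 pain and sleep-interference scores, Table 1), consent is given and the supervisor agrees.
2. Before randomisation, the physician sets the length of absence from Table 2 symptoms, clinical findings and Table 3 information (Interventions).
3. Allocation becomes known during the same visit (Blinding).
4. The questionnaire is sent directly after recruitment. Its workload part is placed after the visit, and symptoms and background variables travel with it (Outcomes).
5. Part-time work starts the next day (Interventions).

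Steps 2 and 4 both concern Table 2 and Table 3 variables. The article does not say which set of values is the baseline.

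**Which variables have a pre-allocation source**

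- Yes: pain and sleep interference (eligibility); pain site and physical examination (visit); diabetes and cardiovascular disease (physician's interview); previous sick leave (occupational health data base).
- None described beyond the general statement in step 2: Oswestry, Quick DASH, COAT, depression, EQ-5D, fear avoidance, psychosocial factors, justice, effort-reward imbalance and workload. The article does not say outright that the three function scales are in the internet questionnaire. That is inferred from their being questionnaires with no other collection described.
- Interference with work (0–10, Table 2) lies between. It may be asked at the visit, but eligibility does not require a score.

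**Effect on the analysis**

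Let the true effect be zero, with equal follow-up means in both arms. Let the first score be shifted by s in one arm only, and let the correlation between first and follow-up score be ρ with equal SDs.

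- Change score: contrast = (difference at follow-up) − (difference in first score) = 0 − s = −s.
- ANCOVA: contrast = 0 − ρ × s = −ρs.
- Follow-up only: contrast = 0.
- Pre-allocation score: s = 0, so all three are zero.

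The article gives no s, SD or ρ. As an illustration, assume SD 2 on a 0–10 scale, s from 0.25 to 1.0 points and ρ from 0.3 to 0.7. Simulated values are in brackets; for the change score they span the three values of ρ.

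| s (points) | s/SD | Change score, −s | ANCOVA, ρ = 0.3 | ANCOVA, ρ = 0.5 | ANCOVA, ρ = 0.7 |
|---|---|---|---|---|---|
| 0.25 | 0.125 | −0.25 (−0.251 to −0.255) | −0.075 (−0.077) | −0.125 (−0.129) | −0.175 (−0.179) |
| 0.5 | 0.25 | −0.5 (−0.486 to −0.505) | −0.15 (−0.141) | −0.25 (−0.251) | −0.35 (−0.346) |
| 1.0 | 0.5 | −1.0 (−0.990 to −1.003) | −0.30 (−0.292) | −0.50 (−0.500) | −0.70 (−0.702) |

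The simulated follow-up-only contrast stayed between −0.005 and 0.007. The exposed function scales are not scored 0–10, so s/SD is the column to carry over to them. The result assumes that the shift affects the first score only. A reporting tendency that lasted through follow-up would also affect the follow-up comparison, and moving the baseline would not cure that.

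**The case against.** **The visit may already supply the baseline.** Pain and sleep scores are needed for eligibility, and Table 2 symptoms and Table 3 information are said to be used before randomisation. This stands for pain and sleep. A reader might infer from the questionnaire schedule that all baseline symptoms are post-randomisation, and the article does not support that. It does not rescue the function scales, for which no collection at the visit is described.

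**Recruitment could mean consent, before allocation.** The wording alone allows this. However, workload data are placed after the visit and share the questionnaire with the symptoms, while allocation is opened during the visit.

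**The gap is short.** The questionnaire goes out at once and work starts only the next day, so exposure to work affects delayed replies only, and no response times are given. Stable items such as education or job seniority are unlikely to move. This stands: the values can bias, and the article does not show that they do. Symptoms and function are more exposed than depression, EQ-5D, fear avoidance or psychosocial scores.

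**The reach is limited.** Time to return to regular work and total sick leave days use no baseline score. Subgroups by previous sick leave or pain site rest on records or the visit. This also stands.

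**Missing waves.** A reader might infer from the repeated-measures general linear model that anyone with a missing wave is dropped. The article states no such rule, and missing-data handling is commonly left to the analysis plan.

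**Conclusion.** The concern holds in a limited form. As written, the article labels as baseline a set of self-report scales that appear to be obtained only after allocation is known, and it does not reconcile this with the use of Table 2 and 3 information before randomisation. Affected are the change analyses of the function scales, the disability reduction in the economic evaluation so far as it uses a score without a visit value, and the baseline-disability subgroup. The calculation of the main outcomes and the subgroups taken from records or the visit are not affected.

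The size and direction are unknown. The rule is a bias of about s for change scores and ρs for ANCOVA, and zero with a pre-allocation score. It rests on two assumptions: that the function scales are collected only by questionnaire, and that knowing the group shifts the first answer differently by arm. A reader might want to turn this into a false-positive rate for the pain score. The documents give no shift or SD for that, and pain is a variable for which eligibility already requires a pre-allocation value.

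This should be corrected, but it does not threaten the trial's main comparison.

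**What to change.** **For participants still to be enrolled.** Have the employee complete the symptom and function scales before the envelope is opened, for example while the supervisor is being contacted, and say so in the Interventions and Outcomes sections. The cost is some visit time and a change in logistics, because the article now delivers the questionnaire by internet or telephone. Enrolment was planned to run from January 2008 to July 2009, so later participants could still benefit.

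**For those already enrolled (analysis only).**

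- Use the pain and sleep-interference scores from the visit as baseline, provided the scores were recorded and not only checked against the cut-off.
- Treat the first questionnaire as an early follow-up measurement.
- Compare function scales between arms at follow-up without adjusting for the first questionnaire. Compared with adjusting for a valid baseline, this multiplies the variance by 1/(1 − ρ²): 1/0.91 = 1.10 at ρ = 0.3, 1/0.75 = 1.33 at ρ = 0.5 and 1/0.51 = 1.96 at ρ = 0.7. Adjusting for the visit pain score may recover part of the loss.
- Do not define the baseline-disability subgroup from the first questionnaire.

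**In the text.** Reconcile the Interventions and Outcomes sections by stating, for each Table 2 and Table 3 variable, whether it is recorded before or after allocation and which value serves as baseline. This costs a wording change.
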